**Figure 8. LENA Data Report Example**

[figure not shown]

## 8.2 SAFETY AND OTHER ASSESSMENTS

Because this study is of an educational intervention, study-related adverse events (AEs) and serious adverse events (SAEs) are not expected. Given the minimal risk of the study, the study team will not solicit AEs or SAEs. However, the study team will provide all participants with a phone number to report AEs and SAEs.

The study team will track severe AEs and SAEs that are potentially study related.

## 8.3 ADVERSE EVENTS AND SERIOUS ADVERSE EVENTS

### 8.3.1 DEFINITION OF ADVERSE EVENTS (AE)

An AE is defined as any untoward occurrence associated with the use of an intervention in humans, whether or not considered intervention-related (21 CFR 312.32 [a]). We include a list of potential AEs in Section 8.3.3.3; however, we will only record severe AEs (defined below in Section 8.3.3.1).

### 8.3.2 DEFINITION OF SERIOUS ADVERSE EVENTS (SAE)

We will consider an AE or suspected adverse reaction "serious" if, in the view of the PIs, the medical monitor, the DSMB, or the sponsor (the DCOC of the ECHO ISPTN), it results in any of the following outcomes:

- Death.
- A life-threatening AE.
- Inpatient hospitalization or prolongation of existing hospitalization.
- Persistent or significant incapacitation or substantial disruption of the ability to conduct normal life functions.

- A congenital anomaly or birth defect.

Important medical events that may not result in death, be life-threatening, or require hospitalization may be considered serious when, based upon appropriate medical judgment, they may jeopardize the participant and may require medical or surgical intervention to prevent one of the outcomes listed in the SAE definition. Examples of such medical events include allergic bronchospasm requiring intensive treatment in an emergency room or at home, blood dyscrasias, convulsions that do not result in inpatient hospitalization, or the development of drug dependency or drug abuse.

---

### 8.3.3 CLASSIFICATION OF AN ADVERSE EVENT

---

#### 8.3.3.1 SEVERITY OF EVENT

These are the guidelines to describe the severity of AEs for the current study:

**Mild** events require minimal or no treatment and do not interfere with the participant's daily activities.

**Moderate** events result in a low level of inconvenience or concern with the therapeutic measures. Moderate events may cause some interference with daily functioning.

**Severe** events interrupt a participant's usual daily activity and may require systemic drug therapy or other treatment. Severe events are usually potentially life threatening or incapacitating. Of note, the term "severe" does not necessarily equate to "serious."

---

#### 8.3.3.2 RELATIONSHIP TO STUDY INTERVENTION

All severe AEs and SAEs must have their relationship to the trial intervention assessed by the site PI or a qualified clinician, who examines and evaluates the participant based on temporal relationship and their clinical judgment. We will grade the degree of certainty about causality by using the categories below.

**Related.** We know the AE occurred with the trial intervention, there is a reasonable possibility that the trial intervention caused the AE, or there is a temporal relationship between the trial intervention and the AE. Reasonable possibility means that there is evidence to suggest a causal relationship between the trial intervention and the AE.

**Not Related.** There is not a reasonable possibility that the administration of the trial intervention caused the event, there is no temporal relationship between the trial intervention and event onset, or there is an established, alternate etiology.

---

#### 8.3.3.3 EXPECTEDNESS

The site PIs will be responsible for determining whether a severe AE or SAE is expected or unexpected. A severe AE or SAE will be considered unexpected if the nature, severity, or frequency of the event is not consistent with the risk information previously described for the trial intervention.

Potential events could include:

- anxiety
- Respiratory infections:
  - Common cold, influenza, RSV etc.
- Gastroenteritis or associated illness
- Allergies
  - Respiratory, skin, eyes etc.
- Other common infections
  - Eyes, ears, skin, throat, UTIs etc.

---

#### 8.3.4 TIME PERIOD AND FREQUENCY FOR EVENT ASSESSMENT AND FOLLOW -UP

The study team will provide participants with a telephone number to report severe AEs or SAEs.

Because this minimal-risk study is for an educational intervention, the study will not actively solicit AEs or SAEs. When a site coordinator or site PI learn of a severe AE or SAE, they will refer participants to their primary care physician. The site coordinator will record the severe AE or SAE in the appropriate EDC system and track it.

The site coordinator will record severe AEs, as described in the next section and in the MOP. Severe AE data collection typically includes event description, time of onset, if available, resolution time and day, if available, and operational PI's assessment of severity, relationship to study participation or intervention (assessed only by those with the training and authority to make a diagnosis), and time of resolution/stabilization of the event. The site coordinator must appropriately document severe AEs occurring during the trial, regardless of relationship to the trial. The DCOC safety personnel will track severe AEs until one of the following criteria are met: resolution, the condition stabilizes, the event is otherwise explained or is judged by the site investigator to be no longer clinically significant, or the participant is withdrawn from the study. DCOC safety personnel will follow all SAEs by asking about the SAE every 14 days until resolution or until the site investigator determines the event to be chronic, or until the participant is stable. The DCOC may request other supporting documentation of the event and should be provided as soon as possible.

Site coordinator will document changes in a severe AE in the source document and EDC to allow an assessment of the duration of the event. Severe AEs characterized as intermittent require documentation of onset and duration of each episode.

Participants may report severe AEs for 7 days after completing study procedures and SAEs for 30 days after completing study procedures. Site coordinators and/or DCOC safety personnel will record and track according to this protocol and DCOC standard operating procedures (SOPs).

---

#### 8.3.5 ADVERSE EVENT REPORTING

Site coordinators or the study team will record severe AEs in the EDC system, include them in the statistical analysis, and follow the reporting procedures outlined in the study-specific MOP. The MOP section on reporting severe AEs will encompass the requirements of:

1. The cIRB's policies and procedures,
2. SOPs for the Streamlined, Multisite, Accelerated Resources for Trials IRB Reliance platform (SMART IRB),

3. ICH E6(R2), Good Clinical Practice: Integrated Addendum to ICH E6(R1): Guidance for Industry, and
4. The local IRB's policies and procedures, when applicable.

If there are discrepancies between the procedures, we will follow the most stringent of the requirements.

If this study is deemed to be greater than minimal risk, or the cIRB otherwise requires a continuing review report, the DCOC will report severe AEs to the cIRB at the time the continuing review is submitted. The DCOC will report to the cIRB at UAMS, as specified in the study-specific IRB communication plan, which is based on recommendations of SMART IRB. Sites will also report severe AEs to the local IRB, per local IRB policies and procedures, and make them available to the sponsor (the DCOC) on a continuing basis through the EDC system. We will report to the DSMB, per the DSMB charter.

The study-specific MOP will describe the details of the reporting structure and additional details related to timelines for reporting.

---

### 8.3.6 SERIOUS ADVERSE EVENT REPORTING

The site investigator or qualified delegate will immediately report to the appropriate entities (which may include the DCOC, NIH, DSMB, and local and/or reviewing IRBs) any SAE when required to do so based on that entity's policies and procedures. Reports need to include the information required by the entities policies and procedures. Study endpoints that are SAEs (e.g., hospitalizations) must be reported in accordance with the protocol unless there is evidence suggesting a causal relationship between the study intervention and the event (e.g., death from anaphylaxis). In that case, the investigator must immediately report the event.

All SAEs will be followed until satisfactory resolution or until the site investigator deems the event to be chronic or the participant is stable. Other supporting documentation of the event may be requested by the DCOC and should be provided as soon as possible.

The DCOC will ensure the summary and report of SAE data to the cIRB in time for consideration at the next continuing review. The DCOC will also create and provide any SAE data summaries requested by the monitors or specified in the DSMB charter. The site PI will be responsible for following their local institution's requirements.

The study-specific MOP has additional details.

---

### 8.3.7 REPORTING EVENTS TO PARTICIPANTS

We will notify participants of those trial-related (or potentially trial-related) SAEs that may affect their willingness to continue with the trial or the future health of the primary caregiver or child. Any of the following can determine if study personnel should contact participants: the cIRB, the medical monitor, the DSMB, the DCOC, NIH, or the PIs. The person or oversight body that makes the determination will inform the DCOC, which will instruct the site investigators and coordinators to contact the participants consented through their site.

The site study team will record any contact with participants, if necessary, in the EDC system or trial log.

## 8.4 UNANTICIPATED PROBLEMS INVOLVING RISKS TO SUBJECTS OR OTHERS (UPIRTSO)

### 8.4.1 DEFINITION OF UPIRTSO

Unanticipated problems (UPs or UPIRTSOs) involving risks to participants or others include, in general, any incident, experience, or outcome that meets all the following criteria:

- Unexpected in terms of nature, severity, or frequency given (a) the research procedures described in the protocol-related documents, such as the Institutional Review Board (IRB)-approved research protocol and informed consent document; and (b) the characteristics of the participant population being studied;
- Related or possibly related to participation in the research (“possibly related” means there is a reasonable possibility that the incident, experience, or outcome may have been caused by the procedures involved in the research); and
- Suggests that the research places participants or others at a greater risk of harm (including physical, psychological, economic, or social harm) than was previously known or recognized.

A UPIRTSO is not necessarily an AE or an SAE.

Examples of UPs/UPIRTSOs that are not an AE or SAE, but which would need to be reported include:

- Breach of confidentiality
- Manufacturer recall of equipment used in the protocol

The study-specific MOP provides additional details.

### 8.4.2 UPIRTSO REPORTING

The site investigator will report UPs (UPIRTSOs) – and potential UPIRTSOs - to the DCOC (which will in turn report to the reviewing (UAMS) IRB), to their local IRB as well as to any other persons or groups noted in the DSMB charter. Reports to NIH and the DSMB will be made by following the chain of notification.

Reporting must follow the study-specific IRB communication plan, local IRB policies and procedures, and the UAMS IRB contemporaneous policy, 10.2., *Events that must be reported to the IRB and IRB Actions*, which is available via <https://irb.uams.edu/irb-policies/current-irb-policies/>.

As of the writing of this section of the protocol (09/12/2023), UAMS IRB reporting requirement per policy 10.2 are:

| UPIRTSO Reporting Requirement |                                                               |
|-------------------------------|---------------------------------------------------------------|
| Unanticipated Problem         | Required Reporting Time to UAMS IRB                           |
| Death or life-threatening     | Immediately to IRB office or IRB Chair                        |
| All other events              | Within 10 days of event or notification of event if non-local |

Reports of potential UPIRTSOs typically require the following information:

- Protocol identifying information: protocol title and number, PI’s name, and the IRB project number
- Event date
- Event location
- Nature of the risk

- How the risk relates to research
- A detailed description of the event, incident, experience, or outcome
- A description of any changes to the protocol or other corrective actions that have been taken or are proposed in response to the UP

If the UAMS IRB determines the issue is, indeed, a UPIRTSO, the DCOC will notify persons and entities as required by UAMS IRB policies and procedures, the study-specific communication plan, and the DSMB charter.

The cIRB will report the issue to the OHRP, and other entities, per the policies of the cIRB.

---

#### 8.4.3 REPORTING UNANTICIPATED PROBLEMS TO PARTICIPANTS

For reporting UPIRTSOs to participants, we will follow the same procedures as described for reporting SAEs to participants (see Section 8.3.7).

## 9 STATISTICAL CONSIDERATIONS

### 9.1 STATISTICAL HYPOTHESES

**Primary Objective:** Explore preliminary efficacy of TWMB for enhancing the HLE for at-risk families, specifically by examining whether the language-promotion behaviors of caregivers improve from Baseline to Post-Intervention.

**Primary Endpoint:** Improvement in language-promotion behaviors (as measured by LENA CTC and AWC percentile scores) from Baseline to Post-Intervention.

**Hypothesis:** Among caregivers completing TWMB, at least 70% for the sample will demonstrate improvement in language-promotion behaviors from Baseline (Week 1) to Post-Intervention (Week 48).

### 9.2 SAMPLE SIZE DETERMINATION

The primary endpoint is a binary variable of reaching at least a 10% increase in AWC or CTC percentile scores from Baseline (Week 1) to Post-intervention (Week 48). This increase is based on previous language-promotion intervention studies using LENA, which reported statistically significant gains (for intervention versus control) for parent language-promotion behaviors ranging from 10-30%. In terms of clinical relevance, the proposed 10% gain in AWC would be an increase of ~160 adult words per hour, which equates to an increase of ~3 points in child language standard scores on the Bayley Scales of Infant Development and the Preschool Language Scale (proposed two-point increase for every increase of 100 adult words per hour for children age birth to four years-old).

The study is expected to have at least 70% of caregiver participants reaching improvement in language-promotion behaviors at the end of the study. In other words, the targeted rate of improvement in language-promotion behaviors is 70%. We plan a total accrual of up to 86 child-caregiver dyad participants into the study with a goal of having at least 66 dyads enter into phase II of the study. With an estimated phase II attrition rate of 20%, we expect that a total of 53 enrolled child-caregiver dyad participants will complete phase II of the study and hence the effective sample size is 53. Using a two-sided exact test with a significance level of 0.05, we are able to reach 85% power to reject a null rate of improvement at 50%, should the targeted rate of improvement be reached.

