The pre-post intervention design allows us to evaluate participant completion of critical measures that will be used in the future, large-scale RCT. Importantly, it also allows us to estimate expected change in caregiver language-promotion skills in response to the intervention. Since TWMB targets caregiver language behaviors, the design includes a pre-post intervention assessment of the HLE using LENA audio-recordings, which is an objective assessment and the research standard for measuring talk with children. These recordings will come from a small recorder (“talk pedometer”) children wear (in a shirt pocket) for a day at a time. See Section 8.1.2 for details about LENA assessment.

In line with emerging guidance on pilot studies prior to high-quality large-scale efficacy trials, the current study design does not include a control group. This is due to the high likelihood of an underpowered sample in this pilot to detect meaningful differences in the endpoints that will be evaluated in the large-scale RCT. By focusing the pilot on delivering TWMB in both clinics, we can maximize the number of dyads ( $n = 86$ , with goal of having at least 66 dyads able to enter phase II) to obtain a better estimate of variability in intervention response, rather than using resources to conduct underpowered difference tests between conditions for an untested intervention in this setting.

Site study teams will consent dyads and will complete baseline measures prior to the start of TWMB implementation in clinics (or prior to having a WCC visit with TWMB during the intervention period). To gather preliminary evidence that TWMB is effective for families with an inadequate HLE and to avoid ceiling effects in this small sample, we will enroll dyads with baseline LENA scores that are  $\leq 75^{\text{th}}$  percentile compared to age-referenced normative data. Of note, previous data have shown that without intervention, caregiver’s language-promotion behaviors do not show significant change across birth to 48 months of age. Therefore, evidence of change in caregiver’s language-promotion behaviors over the course of the TWMB pilot trial would be meaningful preliminary evidence of TWMB efficacy for the home language environment.

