#### 9.4.2 ANALYSIS OF THE PRIMARY EFFICACY ENDPOINT

The primary endpoint of improvement in caregiver language-promotion behaviors (as measured by LENA) will be summarized using frequency (in %). A 95% confidence interval will be constructed using a Clopper-Pearson exact method. Alternatively, a hypothesized null rate can be tested using a two-sided exact test at a significant level of 0.05.

---

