#### 9.4.8 EXPLORATORY ANALYSES

We will examine barriers to enrollment, including our ability to contact caregivers, the proportion of caregivers that consent to participate in the study, enrollment of caregiver-child dyads, and caregivers' willingness to

complete baseline assessments. We will also examine characteristics related to attrition for caregiver and provider participants. Descriptive statistics will be used in these exploratory analyses.

Caregiver language promotion behaviors (LENA) will be examined and reported descriptively. Child vocalization scores (LENA) will be reported descriptively. We will also examine associations of differences in change in LENA scores with caregiver characteristics (e.g., low, or high baseline LENA scores, education level, SES) using analysis of variance (ANOVA) models or linear regression models.

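### The only primary inference is on an improved/not-improved rate, so the mean LENA change that the pilot is meant to estimate has no prespecified interval; the exact test's power is also 78%, not 85%

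*Protocol*

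**What the plan says.** Section 9.2 makes the outcome dichotomous: "The primary endpoint is a binary variable of reaching at least a 10% increase in AWC or CTC percentile scores", measured from Baseline to Week 48. The hypothesis in 4.1.1 and 9.1 is also a rate: at least 70% of caregivers improve. On size, 9.2 plans accrual "with a goal of having at least 66 dyads enter into phase II of the study", takes 20% attrition, and arrives at 53 completers. The test is named there ("Using a two-sided exact test with a significance level of 0.05"), and the power claimed for it reads: "we are able to reach 85% power to reject a null rate of improvement at 50"%. The alternative is given separately: "the targeted rate of improvement in language-promotion behaviors is 70"%.

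Section 9.4.2 reports the endpoint as a percentage with a Clopper-Pearson 95% interval, or alternatively an exact test against a null rate. It contains nothing else.

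Section 4.2.1 gives the purpose of the pre-post design: "it also allows us to estimate expected change in caregiver language-promotion skills in response to the intervention". It adds that the number of dyads is maximised to estimate the variability of response better.

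The continuous scores appear in two other places. Section 9.4.1 summarises every numerical variable by mean and SD, among other statistics, and says the summaries will inform the future RCT. Section 9.4.8 says: "Caregiver language promotion behaviors (LENA) will be examined and reported descriptively", and relates change in LENA scores to caregiver characteristics by ANOVA or regression, as exploratory work.

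**The concern.** Every completing dyad should have AWC and CTC scores at both time points; 8.1.2 has the standard scores entered in the database. The primary analysis keeps one yes/no from these. A dyad just short of the cut counts the same as one whose talk fell sharply.

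Two things are at stake. The first is purpose. A future RCT on LENA scores would be sized on a mean change and its SD, and 4.2.1 presents the pilot as the source of both. The plan attaches no confidence interval to that change, so its precision is not part of the prespecified inference.

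The second is information. Dichotomising a continuous change usually costs power, and here the power of the chosen test is also overstated.

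The support for the cut is thin as well. The 10-30% gains cited in 9.2 are intervention-versus-control contrasts, not individual thresholds. The clinical-relevance argument concerns adult words per hour only, although CTC alone can qualify a dyad.

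**Working it through.** **Inputs (9.2).** 66 dyads entering Phase 2; 20% attrition, 66 × 0.8 = 52.8, taken as n = 53; null rate 0.50; target 0.70; two-sided alpha 0.05.

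**1. The plan's 85%.** For the two-sided exact binomial test at p = 0.50:
- P(X ≥ 34) = 0.0267. Doubled, this is 0.0534, above 0.05, so 34 does not reject.
- P(X ≥ 35) = 0.0135. Doubled, this is 0.0270, so the test rejects at 35 or more (or 18 or fewer).
- Power at 0.70 = P(X ≥ 35) = **78.4%**.

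Rejecting from 34 would give 85.9% power, but at size 0.053. The stated figure is reproduced by the normal approximation without continuity correction: (0.20 − 1.96·√(0.25/53)) / √(0.21/53) = 1.039, and Φ(1.039) = 85.1%. That is not the exact test named.

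**2. The same contrast on a continuous scale.** This needs assumptions that the protocol does not state: one change score, normal, with a pure location shift, and a null mean at the cut. Then 50% to 70% above the cut is a shift of d = Φ⁻¹(0.70) − Φ⁻¹(0.50) = 0.524 SD. The noncentrality is 0.524·√53 = 3.82 on 52 df, with critical value 2.007. Power is **96.3%**. Part of the 17.9-point difference from 78.4% comes from the exact test using only 0.027 of its 0.05, not from dichotomising.

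**3. How far this depends on the model.** The 70% rate is kept, n = 53, single score, by simulation:

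| Distribution of change | One-sample t-test | Signed-rank |
|---|---|---|
| Normal | 96% | 96% |
| t, 4 df | 83% | 91% |
| t, 3 df | 74% | 90% |
| Laplace | 74% | 85% |

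The planned exact test has 78.4% in every row. The signed-rank test stays above it in these cases; the t-test does not.

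**4. The either-score rule.** Assume bivariate normal changes with equal shifts, and correlation between the AWC and CTC changes from 0 to 0.9 (the protocol gives none). One score tested alone at 0.05 has 86% to 96% power. The mean of the two scores has 99% to 97%.

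**5. Selection at baseline.** Dyads continue only with a baseline score at or below the 75th percentile (4.2.1, 5.1.2). For one normal score truncated there, the baseline mean is −φ(0.674)/0.75 = −0.318/0.75 = −0.424 SD. With retest correlation r and no effect, the expected rise is (1 − r) × 0.424. This is 0.21 SD at r = 0.5 and 0.13 SD at r = 0.7 (r is assumed). A two-sided t-test of mean change against zero would then falsely favour benefit in about 36% and 23% of trials of 53 dyads.

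**The case against.** The plan is consistent with itself: a rate hypothesis, a rate endpoint, a test of a rate, and a sample size for a rate. Replacing the endpoint would change the question, not correct a contradiction. This stands, and it is why the responder rate should remain primary.

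A reader might infer more than the documents support, in four ways:
- **That the cut costs 11 to 18 points of power under the plan's own assumptions.** The plan gives only n, two rates and alpha. The gain rests on the added model in steps 2 to 4. The lower figure is measured against an 85% that the exact test does not reach.
- **That the trial will not yield the expected change at all.** Sections 9.4.1 and 9.4.8 make the mean and SD of LENA scores obtainable descriptively. The gap is the missing prespecified interval.
- **That a group gaining exactly the cut would reject only 2.7% of the time.** That holds for a single measure. Under the AWC-or-CTC rule, if both measures gain the cut, normal changes put 57%, 67% or 75% of dyads above it at correlation 0.9, 0.5 or 0. The planned test then rejects in about 12%, 60% or 95% of trials.
- **That mean change tested against zero would be better primary evidence.** Step 5 shows zero is not a neutral null here, and such a test would drop the 10% threshold.

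It can also be said that an interval is detail for the SAP. That has some force. But 9.4.1 has the SAP detail the analyses outlined in the protocol, and an inferential analysis of mean change is not among them, although 4.2.1 makes that change a purpose of the design.

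**Conclusion.** The point holds in limited form. The protocol confines primary inference to a responder rate and leaves the change it says it wants to estimate without a prespecified interval. This follows from the text and needs no power model.

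The power of the named test is 78.4%, about 7 points below the stated 85%; this is exact for 53 dyads, 50% versus 70%, at two-sided 0.05. The information lost by the cut could be large, 96% against 78% with one normal change score, but its size is not established. It depends on the distribution of change, the AWC-CTC correlation and the test used, and with heavy tails the t-test does worse than the planned test. The case supports adding an analysis, not replacing the primary one.

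**What to change.** In 9.4.2, keep the responder rate with its Clopper-Pearson interval as primary. Add, as a prespecified inferential analysis, the within-dyad mean change from Baseline to Post-Intervention in AWC and in CTC standard scores, each with a 95% CI and SD, and a signed-rank sensitivity analysis.

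State beside it that the entry rule at the 75th percentile puts regression to the mean into both the mean change and the responder rate, so a test against zero is not by itself evidence of effect.

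In 9.2, restate the power of the exact test with 53 completers as about 78%. Carry all three changes into the SAP before data lock.

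The cost is amended wording and a little more analysis; no new data, visits or dyads. The downside is a less favourable stated power.

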### 5.1.2 CAREGIVER-CHILD PARTICIPANT INCLUSION CRITERIA

For this study, each child-caregiver dyad will consist of:

1. A caregiver who will receive TWMB during routine WCC visits for their child at participating clinics, and
2. The child of the above caregiver for whom the WCC visits are conducted.

A potential caregiver participant must meet all the following inclusion criteria to enroll in the study:

1. Be the age of majority, or older, as defined by the state of residency.
2. Able to complete study measures in English.
3. Have the legal authority to consent to participate for themselves and to consent on behalf of their child.

To proceed to the follow-up portion of the study the caregiver (dyad) must have a LENA baseline assessment score that is  $\leq 75^{\text{th}}$  percentile compared to a child's age-referenced normative data.

A potential child participant must meet all the following inclusion criteria to be enrolled in the study:

1. Receive WCC at a participating clinic from a participating provider.
2. Be zero to nine months (+ 0–30 days) old at enrollment.
3. Was born at full term ( $> 37$  weeks gestation).
4. Was born in a singleton birth (i.e., was the only child delivered during the birth).

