**Figure 7. LENA “Talk Pedometer” Recorder and Vest With Instructions**

[figure not shown]

LENA is the research standard for measuring talk with children because it is user-friendly and widely used in the field to successfully collect data from families of diverse characteristics. Since the technology became available in 2008, LENA data have been published in 150+ observational and interventional studies involving many hundreds of children. LENA is family-friendly and has been used successfully in many large-scale studies with infants and toddlers using the methods we will use.

Study staff will mail the LENA recorder and vest to the family; alternatively, the LENA recorder may be provided to the family at a clinic visit. Study staff will then complete a short phone call with the family to walk through how to use the device and answer any questions (simple instructions are also provided with the device, see **Figure 7**). If the family opts for electronic communications, the family will get an electronic link and be able to complete the review and questionnaire electronically. Families will be asked to complete 2 day-long recordings during a period when the child is in the home setting (i.e., not at daycare), turning on and putting on the device at the start of the day when the child first wakes up and leaving it on for 12-16 hours. The LENA recorder can remain turned on and be taken off and left nearby during bath or naps, if needed. The device automatically turns off when the maximum recording time is reached. Families will be asked where the recording was obtained. Families will complete a recording on two separate days during Baseline (i.e., Phase 1); Phase 2 participants will complete a recording on two separate days again during the Post-Intervention Assessment phase.

Participants will be asked to complete questionnaires at the end of each recording day. These questionnaires will ask about where the child was (based on 2-hour intervals) during the recording time period, what the child was doing, and who was with the child during the recording time period. A paper version of the question will be sent with the LENA device. The adult participant will have the option to answer the questions electronically, by phone, or by sending the completed paper questionnaires back with the LENA devices (see below).

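### The 50% null in section 9.2 is not justified as the no-intervention rate, and on the literal endpoint rule chance improvement probably exceeds it

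*Protocol*

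**What the plan says.** Protocol section 9.2 gives the only operational definition of the endpoint: "The primary endpoint is a binary variable of reaching at least a 10% increase in AWC or CTC percentile scores from Baseline" to Week 48. On size and power it says "the targeted rate of improvement in language-promotion behaviors is 70" per cent. It continues "Using a two-sided exact test with a significance level of 0.05" and "we are able to reach 85% power to reject a null rate of improvement at 50" per cent, with 53 dyads expected to complete. No reason is given for 50%.

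Section 9.1 words the endpoint differently: "Improvement in language-promotion behaviors (as measured by LENA CTC and AWC percentile scores) from Baseline to Post-Intervention". Sections 1.1, 3 and 4.1.1 also join the two scores with *and*; only 9.2 uses *or*.

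Section 5.1.2 restricts Phase 2: "To proceed to the follow-up portion of the study the caregiver (dyad) must have a LENA baseline assessment score that is" at or below the 75th percentile. It does not say whether the cut applies to AWC, CTC or both. Section 4.2.1 explains that there is no control group. It also reports earlier data in which caregiver behaviours, without intervention, "do not show significant change across birth to 48 months of age", and concludes that change during the pilot would be an early sign that TWMB works.

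Section 9.4.2 leads with the proportion and a Clopper-Pearson interval. It offers an exact test against a null rate as an alternative, without naming the rate.

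**The concern.** In a single-arm study the null rate is the only comparator, so it should be the rate expected with no intervention effect. Three features of the rule in 9.2 push that rate up.

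- A dyad has two chances, because either score may rise.
- The baseline score that admits a dyad to Phase 2 is also the reference for change. Removing high baseline values makes the remaining group drift upward on remeasurement.
- If 10% is relative, the required step is small at low percentiles. From the 20th percentile it is 0.10 × 20 = 2 points.

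The statement in 4.2.1 about no significant change concerns average behaviour across ages. It does not say how often an individual dyad moves up by 10% on one of two scores measured on one or two days. If that happens in more than half of untreated dyads, rejecting 50% could be read as preliminary efficacy when noise and selection produced it.

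**Working it through.** **Inputs from the protocol.** n = 53 (66 × 0.80 = 52.8), null 0.50, target 0.70, two-sided exact test at 0.05 (9.2); baseline cut at the 75th percentile (5.1.2).

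**The plan's own figure.** For X ~ Binomial(53, 0.5), P(X ≥ 34) = 0.0267, two-sided p = 0.053. P(X ≥ 35) = 0.0135, two-sided p = 0.027. The equal-tailed test therefore needs 35/53 (66%), and its power at 0.70 is P(X ≥ 35 | 0.70) = 78.4%, not 85%. The normal approximation gives 85.05%:

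Φ[(0.20·√53 − 1.96·0.5)/√(0.7·0.3)]

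An unequal-tailed region (≤18 or ≥34, size 0.040) gives 85.9%. This is a separate matter. I use 35/53 below; a threshold of 34 would make every chance figure larger.

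**Chance of success as a function of the no-effect rate p:** P(X ≥ 35 | 53, p).

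| p | 0.50 | 0.55 | 0.56 | 0.60 | 0.65 | 0.70 |
|---|---|---|---|---|---|---|
| chance | 1.4% | 6.9% | 9.0% | 22.6% | 50.0% | 78.4% |

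The nominal 2.5% upper-tail error is passed once p exceeds about 0.517.

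**No-effect rate.** The protocol gives no correlations, so these are assumptions: age-normed AWC and CTC scores are normal with the same mean at both visits (the norm mean); retest correlation r and AWC-CTC correlation ρ each lie between 0.5 and 0.8; no intervention effect. I simulated 400,000 dyads per scenario. Follow-up z-score = r × baseline z + √(1 − r²) × independent noise with the same ρ; z-scores were converted to percentiles, and the cut and improvement rule applied.

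| Rule | Both scores ≤75th | Either score ≤75th |
|---|---|---|
| *or*, relative 10% | 0.60–0.73 | 0.56–0.66 |
| *or*, 10 percentile points | 0.44–0.62 | 0.41–0.56 |
| *and*, relative 10% | 0.33–0.45 | 0.25–0.39 |

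Requiring both scores to rise by 10 points gives lower rates still.

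**What drives it.** At r = 0.6, ρ = 0.7, relative 10%, both scores under the cut: about 54% improve on a given score and 67–68% on at least one. Without the cut, the either-score rate is 54%. Both the cut and the *or* rule therefore contribute.

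**Sensitivity to the source population.** The summary of changes to version 08 reports more dyads above the 75th percentile than expected. If the source mean is 0.3 SD above the norm, the literal rule with both scores under the cut gives 0.64–0.76 (r 0.5–0.8, ρ 0.5–0.7).

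**Power at a true 0.70 if the null were higher.** Null 0.55 needs 37/53, power 58%. Null 0.60 needs 40/53, power 24%.

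**The case against.** The strongest objection is that the size rests on unsettled wording. A reader might infer that 50% is plainly wrong and that the trial will usually succeed by chance. The documents do not support that. Ten percentile points is a natural reading of 10% on a percentile score, and at a retest correlation near 0.8 it makes 50% slightly conservative. Section 9.2's gloss of about 160 adult words per hour does not settle the reading. Under the *and* wording of four other sections, the no-effect rate stays below 50% in every scenario run. This objection stands and limits the claim about size. It does not supply a reason for 50%, and 9.2 is the only place that defines a responder.

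Second, this is an exploratory pilot before a randomised trial. Section 9.4.2 puts estimation first, and the 50% appears only in the sample-size paragraph. That lowers the stakes. But 9.2 powers a formal test, and 4.2.1 invites an efficacy reading of change.

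Third, the cut removes only dyads above the 75th percentile, so it would overstate matters to call the sample selected for low scores. The upward regression is real but moderate.

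Finally, a reader might infer that the two baseline recording days could supply the correct null, since section 8.1.2 says: "Families will complete a recording on two separate days during Baseline (i.e., Phase 1"). They cannot do so reliably. In simulations with slow drift, the day-to-day rate was 0.58 against a true 48-week rate of about 0.66. With no drift and two-day averaging it was 0.69 against about 0.63. With at most 86 dyads its 95% interval is also about ±10 points (1.96·√(0.65·0.35/86) = 0.10).

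**Conclusion.** The concern holds in a limited form. No section justifies 50% as the rate expected without TWMB, and I am confident of that. On the literal 9.2 rule the no-effect rate is about 0.56 to 0.73. This assumes normal scores at the norm mean and both correlations between 0.5 and 0.8. The chance of passing the test with no effect is then 9% at the low end and above 78% at the high end. Confidence in the size is moderate, because the correlations, the meaning of 10%, the score to which the cut applies and the *and*/*or* conflict are all open. Some of those readings put the rate below 50%. The point should be fixed before analysis. It does not invalidate the pilot as an estimation exercise.

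**What to change.** 1. Reconcile *or* in 9.2 with *and* in 1.1, 3, 4.1.1 and 9.1. State whether 10% is relative or percentile points, and whether the 75th-percentile cut applies to AWC, CTC or both.
2. In 9.2 and 9.4.2, remove 50% as the efficacy null or justify it for the final rule. Report the proportion with its Clopper-Pearson interval as descriptive, and state that rejecting 50% alone is not evidence of efficacy. In 4.2.1, qualify the sentence that treats change during the pilot as an early sign of efficacy.
3. As a supportive reference only, report how often dyads improve between the two baseline days under the same cut and rule, with an interval. State that it cannot capture 48-week drift and may err by 5 to 9 points in either direction under the relative rule.

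The cost is wording in the protocol and the analysis plan; no new data are needed. The pilot then makes a weaker efficacy claim. If a higher null is adopted, power at 70% with 53 dyads falls to 58% (null 0.55) or 24% (null 0.60).
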